### Measures and Data Collection

#### YouthCHAT

YouthCHAT covers 10 domains: smoking, drinking, recreational drug use, problematic gambling, depression, anxiety, sexual health, exposure to abuse, anger management, and physical activity. In the case of positive screens, branching logic links users to validated assessment tools including SACS for drug and alcohol use, PHQ-9 for depression, and GAD-7 for anxiety. For the purpose of this project, three new domains have been added to YouthCHAT related to diet, body image, and bullying. Questions related to these domains have been developed based on existing validated tools and have been trialled with student focus groups prior to initiation of the study comparing YouthCHAT with HEEADSSS. Interested readers are welcome to contact the authors for the complete list of YouthCHAT questions.

#### HEEADSSS

HEEADSSS is a clinician-administered, interview-based assessment of youth that can identify mental health and substance use problems [18,19]. It covers the domains of Home, Education/employment, Eating, Activities, Drugs and Alcohol, Sexuality, Suicide/depression, and Safety. It is currently administered by trained school health nurses to all Year 9 students in low-decile schools and some attendees at primary care and pediatric services in New Zealand.

#### Administrative Data

Administrative data such as staff time to complete screening/assessments, psychosocial issues identified via HEEADSSS and YouthCHAT, and referrals made based on positive screens will be collected.

#### Participant Survey

Following completion of YouthCHAT, participants at Starship and Tamaki College will be asked to complete a survey comprised of Likert scales, free-text options, and forced-choice questions on the acceptability and utility of YouthCHAT.

#### Clinician Interviews

Taped and transcribed semistructured interviews with the participating school, Starship, and hospital staff will be conducted (N=10-15). Interviews will focus on perceptions of the utility and acceptability of YouthCHAT (both settings) and comparability with HEEADSSS (Tamaki only) and will be conducted in person or by telephone as preferred by participants.

#### Focus Groups

Two taped and transcribed student focus groups to advise on the face validity and wording of the newly added YouthCHAT modules were conducted at Tamaki College during the first phase of the research. An additional four taped and transcribed student focus groups that address acceptability and utility of the assessments will be conducted at Tamaki College at the end of the school year during the second phase.

### Procedure

During the first phase, screening questions to address the HEEADSSS domains of eating issues, conduct problems/bullying, and resilience/strengths were selected based on existing validated tools sourced through the peer-reviewed literature. These questions were adapted to the New Zealand youth context using focus groups with high school students. Students were asked to judge whether the questions make sense, explain what they think the questions are asking, identify any words or phrases they find unclear, and suggest alternative youth-friendly language. They were also asked to indicate the order in which the questions should appear and enhancements followed majority opinion. In the spirit of biculturalism, at least one focus group was undertaken with only Māori young people to identify any culturally relevant viewpoints, issues, or concerns. Focus groups were audiotaped, confidentially transcribed, and suggestions categorized and tabulated. The resulting additional modules were programmed into YouthCHAT.

During the second phase, a counterbalanced RCT of YouthCHAT and HEEADSSS will be undertaken with high school students. During this study, one group will receive YouthCHAT before HEEADSSS assessment (Condition 1), and the other HEEADSSS assessment before YouthCHAT (Condition 2) and findings from YouthCHAT and HEEADSSS assessment will be compared. In addition, the acceptability and utility of YouthCHAT will be evaluated in two settings—the high school where YouthCHAT and HEEADSSS assessments are undertaken and a tertiary pediatric hospital setting where young people aged 13-18 years with long-term physical conditions are attending pediatric outpatient appointments. Following the use of YouthCHAT by both audiences, focus groups will be undertaken to identify positive feedback, issues, and concerns regarding the electronic screener. Once again, at least one focus group will be undertaken in each setting with only Māori young people to identify any culturally relevant viewpoints, issues, or concerns. In addition to feedback from young people, feedback regarding appeal and utility will be sourced from school nurses at the high school and pediatricians and specialist nurses at the pediatric hospital.

Any focus group participants at the tertiary pediatric hospital who are distressed or develop psychosocial concerns during or following the study will be referred to the hospital-based consult liaison (mental health) service for further assessment and management, in a similar manner to what would occur as part of usual care. Within the high school setting, stepped-care resources and a clinical pathway (algorithms relating to domain and severity of identified problem) will be provided to augment usual care options. These include self-help resources (helplines, psychoeducation and information sheets, websites, and e-therapies), clinician interventions (medications and brief interventions), local community agencies, and referral to adolescent secondary care mental health and drug and alcohol services.

### Data Handling

HealthLink, an electronic data management system, will provide secure storage of all YouthCHAT screening data. It will also enable encrypted secure data transmission to the clinic’s MedTech32 practice management system (PMS) software by the same private network used for their electronic referrals solution. Clinical staff will access their YouthCHAT summary reports directly from the website. This allows a brief version to be cut and pasted into clinical notes, or a PDF generated to attach to the patient file. HEEADSSS data will be managed as per standard care via the school nurse and his/her team. All HEEADSSS data are entered into the PMS, with a summary report provided to the Ministry of Health. HEEADSSS data will need to be manually inputted into a Microsoft Excel spreadsheet by a research assistant. Each YouthCHAT generates a unique code for each participant. This code will be transferred by the school nurse into the PMS HEEADSSS file for data-matching. Thus, research data will be anonymized and de-identified prior to being analyzed.

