Home, Education/employment, Eating, Activities, Drugs and Alcohol, Sexuality, Suicide/depression, Safety (HEEADSSS) assessment is a clinician-administered, interview-based assessment of youth that can identify mental health and substance use problems [18,19]. Currently, all Year 9 (13-14 year olds) students in low-decile schools (those with the highest proportion of students from low socioeconomic communities), and some attendees at primary care and pediatric services in New Zealand are screened for well-being via HEEADSSS assessment. While HEEADSSS assessment offers a straightforward, holistic, and gradual approach to assessing young people across many domains, it is a face-to-face assessment, not a screening tool. Drawbacks include its lack of validation for problem identification, the cost of resourcing, time required for its administration (up to 45 minutes), and variability of assessment depending on the skill and experience of the assessor. In many high schools, it takes a full school year and more than one school nurse to screen all Year 9 students (personal communication [name]). In pediatric settings around New Zealand, routine screening for psychosocial problems is not usually undertaken and HEEADSSS assessments are conducted by some medical and nursing staff in an ad hoc manner.

The Youth version of the electronic Case-Finding and Help Assessment Tool (YouthCHAT) [20,21] is a self-report screening tool that covers ten domains: smoking, drinking, recreational drug use (based on the Substances and Choices Scale [SACS]) [22], problematic gambling, depression (based on the Patient Health Questionnaire – Adolescent Version [PHQ-A]) [23], anxiety (based on the Generalized Anxiety Disorder scale, 7 item [GAD-7]) [24], sexual health, exposure to abuse, anger management, and physical activity. For each positive domain screened, there is a “help” question that asks participants if they would “like help today,” “want help, but another time,” or “don’t want help.” Responses to the “help” question support conversations between young people and their health providers about the issues they would like addressed, which facilitates shared decision making, with increased likelihood that real sustained changes will be made.

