YouthCHAT provides summary reports to authorized school/health clinic staff plus a guide to stepped-care management from self-help through to secondary care. It is a rapid screening system (taking 5-15 minutes to complete) and can be conducted on any electronic device. YouthCHAT has a 14-year history of development in primary care, youth, and school clinics [20,21,25-31]. Recently, it was successfully implemented in a rural school clinic and favorably received by both young patients and clinic staff. Evidence indicates that students are more likely to disclose information about challenges they are facing through electronic means than an initial in-person assessment [32].

As a validated and rapid screening tool, YouthCHAT has the potential to overcome barriers associated with HEEADSSS assessment, while providing a similar holistic assessment of mental health and lifestyle issues. Additionally, as YouthCHAT collects and provides electronic data, the additional paperwork that HEEADSSS requires is not needed. YouthCHAT may be a more efficient screener and serve as a useful substitute or precursor to HEEADSSS assessment. YouthCHAT currently screens for all HEEADSSS domains except three: eating issues, conduct problems/bullying, and resilience/strengths. Additional screening questions to cover these domains have been added, based on those available in the existing literature, with appropriate wording advised by high school students, including those of Māori and Pacific Island descent via focus groups to ensure the updated version of YouthCHAT is appropriate for young people from all major ethnic groups in New Zealand.

The aims of this study are to (1) validate three additional YouthCHAT domains against comparable HEEADSSS domains, (2) ascertain the acceptability and utility of YouthCHAT for children with long-term physical illness and high school students, and (3) compare the performance of YouthCHAT and HEEADSSS in the high school setting.

We hypothesize that a version of YouthCHAT matched to HEEADSSS for all domains will be an acceptable alternative to a HEEADSSS assessment to both young people and the clinical staff conducting the screen. We further hypothesize that screening using YouthCHAT, followed up by a targeted or full HEEADSSS assessment where indicated, will be a much more streamlined and efficient system to enable identification and intervention of young people at risk.

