### Participants and Recruitment

During the first phase, up to 20 senior students aged 16-18 years from Tamaki College, a low-decile high school in Auckland, New Zealand, were invited to participate in focus groups to update YouthCHAT via flyers sent to their school. These students were chosen as they were all able to give their own consent.

During the second phase, approximately 150 Year 9 students (aged 13-14 years) from the same high school will be invited to participate in the RCT and school-based acceptability evaluation via letters will be sent to their parents. Parents may use a reply-paid form to opt out of the study if they do not wish their children to participate. However, regardless of this, all students will receive mandatory HEEADSSS assessments (as is routine for all students in this class). Students who choose to participate in the study will be randomly assigned to one of the two conditions (YouthCHAT followed by HEEADSSS assessment or HEEADSSS assessment followed by YouthCHAT) via a computer-generated random numbers table, with resulting lists provided to clinic staff. Sampling will be consecutive until all enrolled students have completed assessment. All screening will take place in the student health clinic on a desktop computer. A subset of 32 students will be invited to participate in four focus groups, and four school staff (nurses and counsellors) will be invited to complete semistructured interviews on the acceptability, utility, and comparability of YouthCHAT and HEEADSSS assessment. This age group of participants was chosen as it matches the age group of students who routinely receive HEEADSSS assessments in New Zealand low-decile schools.

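### The HEEADSSS interviewer is not described as masked to the YouthCHAT report in Condition 1, and counterbalancing would halve, not cancel, any resulting effect

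*Protocol article*

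**What the plan says.** All references are to the protocol article.

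- **Order (Procedure).** Year 9 students are randomised to YouthCHAT then HEEADSSS (Condition 1) or the reverse (Condition 2), and the findings of the two tools are compared.
- **Interviewer (HEEADSSS).** "It is currently administered by trained school health nurses to all Year 9 students in low-decile schools".
- **Access to the YouthCHAT result (Introduction; Data Handling).** "YouthCHAT provides summary reports to authorized school/health clinic staff", and "Clinical staff will access their YouthCHAT summary reports directly from the website". A short version can be pasted into the notes or a PDF added to the file. No timing relative to the interview is given.
- **Linkage (Data Handling).** For the YouthCHAT code: "This code will be transferred by the school nurse into the PMS HEEADSSS file for data-matching".
- **Knowledge of order (Participants and Recruitment).** Allocation is made "via a computer-generated random numbers table, with resulting lists provided to clinic staff".
- **Assessor dependence (Introduction).** Among the drawbacks of HEEADSSS the article lists "variability of assessment depending on the skill and experience of the assessor".
- **Outcomes (Outcome Variables).** Per-domain detection (present or absent) by each tool and time to complete each tool are both primary outcomes for the school sample.
- **Analysis (Power Calculation and Data Analysis).** t tests, ANOVA and Wilcoxon signed-rank tests are named. An order factor is neither stated nor excluded.

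**The concern.** In Condition 1, the people who conduct and record HEEADSSS belong to the group that can already open the YouthCHAT report. HEEADSSS is a clinician's judgement, so a nurse who knows which domains were flagged may probe them harder or rate them positive more readily.

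This is a realistic route. The Introduction describes the help responses as a basis for conversation with the provider, and it hypothesises a screening sequence of YouthCHAT followed by a targeted or full HEEADSSS. Condition 1 has that same sequence.

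Counterbalancing protects against carry-over that is equal in both directions. Staff knowledge is not: it can alter a clinician-rated interview, but not a questionnaire that the student completes alone.

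The stakes are high because the Discussion says there is no other gold standard. Comparison with HEEADSSS is therefore the main quantitative evidence on detection. The Conclusion would use a finding of comparability to support dropping routine HEEADSSS after a negative screen.

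**Working it through.** The plan gives no figure on this point, so there is none to reproduce. The rates below are assumptions for illustration. The article names no agreement statistic, and kappa is used only to show the size of the effect.

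**1. What counterbalancing removes.** Let D be the true HEEADSSS minus YouthCHAT difference, cH the effect of a prior YouthCHAT on HEEADSSS, and cY the effect of a prior HEEADSSS on YouthCHAT.

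- Condition 1 estimates D + cH.
- Condition 2 estimates D − cY.
- With equal groups (the ratio is not stated), the average is D + (cH − cY)/2.

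The bias vanishes only if cH = cY. The staff-knowledge part enters cH alone, so half of it remains.

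**2. Detection, YouthCHAT detecting more (assumed).** Cells: both positive 10%, YouthCHAT-only 10%, HEEADSSS-only 5%, neither 75%. In Condition 1, suppose nurses pick up half of the YouthCHAT-only cases.

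| | HEEADSSS | YouthCHAT | Gap (points) | Observed agreement | Chance agreement | Kappa |
|---|---|---|---|---|---|---|
| Clean | 15% | 20% | 5 | 0.85 | 0.71 | 0.14/0.29 = 0.48 |
| Condition 1 | 20% | 20% | 0 | 0.90 | 0.68 | 0.22/0.32 = 0.69 |
| Both orders averaged | 17.5% | 20% | 2.5 | 0.875 | 0.695 | 0.18/0.305 = 0.59 |

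**3. Detection, HEEADSSS detecting more.** Swap the discordant cells (YouthCHAT-only 5%, HEEADSSS-only 10%) and keep the same nurse behaviour.

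| | HEEADSSS | YouthCHAT | Gap (points) | Observed agreement | Chance agreement | Kappa |
|---|---|---|---|---|---|---|
| Clean | 20% | 15% | 5 | 0.85 | 0.71 | 0.14/0.29 = 0.48 |
| Condition 1 | 22.5% | 15% | 7.5 | 0.875 | 0.6925 | 0.1825/0.3075 = 0.59 |
| Both orders averaged | 21.25% | 15% | 6.25 | 0.8625 | 0.70125 | 0.16125/0.29875 = 0.54 |

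Agreement rises in both cases. The rate gap shrinks in one and widens in the other.

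**4. A second set of assumptions.** Take prevalence 27% (the article's figure for anxiety and depression), sensitivity 0.6 for HEEADSSS and 0.8 for YouthCHAT, specificity 0.9 for each, and independent errors.

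- HEEADSSS rate: 0.27 × 0.6 + 0.73 × 0.1 = 23.5%.
- YouthCHAT rate: 0.27 × 0.8 + 0.73 × 0.1 = 28.9%.
- Clean gap 5.4 points, kappa 0.36.

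If 25%, 50% or 100% of YouthCHAT-positive, HEEADSSS-negative ratings become positive in Condition 1, the averaged YouthCHAT minus HEEADSSS gap is 3.5, 1.6 or −2.2 points. The averaged kappa is 0.42, 0.48 or 0.59.

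**5. Time.** The planning means are 15 and 45 minutes, a difference of 30. A change of c minutes in HEEADSSS in Condition 1 gives 30 + c/2 averaged over both orders: 22.5 for c = −15, and 37.5 for c = +15. Prior information could shorten the interview or lengthen it, and the article does not settle which.

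**6. What the randomised order can recover.** YouthCHAT in Condition 1 against HEEADSSS in Condition 2 uses only the tool given first, so it is free of cH and cY. With 72 per group and a 20% rate, the 95% half-width is 1.96 × √(2 × 0.2 × 0.8/72) = 0.131. For time, with SDs 30 and 90, the root-mean-square SD is √((900 + 8100)/2) = 67.08 and the standard error is 67.08 × √(2/72) = 11.18. Then 30/11.18 − 1.96 = 0.72, which is 76.5% power at an assumed two-sided 5% level.

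**The case against.** The strongest reply is that the article shows opportunity, not contamination. The access sentence describes how reports are retrieved and filed; it gives no timing and does not say that the interviewing nurse reads one beforehand. Clinical staff is a broad term, and a matching code reveals no result. This stands: the effect is possible, not established.

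Three stronger readings are tempting and are not supported.

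- **That both orders are pooled and the randomised order goes unused.** A reader might infer this from the signed-rank test and from power stated for the two assessments on 144 participants. The article does not state it. Analysis by order may sit in an analysis plan that is not shown, and its absence here is no fault.
- **That a nurse would skip unflagged domains.** All students receive the routine mandatory HEEADSSS (Participants and Recruitment). The targeted interview after YouthCHAT is a hypothesised or future system, not the described trial procedure.
- **That the trial is biased towards comparability.** Steps 3 and 5 show that this does not hold in general for rates or for time. The article also asks whether YouthCHAT is as good as HEEADSSS or better, and extra HEEADSSS positives would count against it on that question.

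It is also fair to say that students may answer YouthCHAT differently after an interview, so cY need not be zero. Counterbalancing deals with whatever part of student carry-over is equal in both directions.

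The unseen analysis plan is only half an answer. It could add results by order, but no analysis can restore a within-student HEEADSSS rating made with the comparator's result in view.

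**Conclusion.** The concern holds in a limited form. The interviewing staff can have the YouthCHAT report in Condition 1, no masking is described, and HEEADSSS is acknowledged to depend on the assessor. Any staff-knowledge effect would act on HEEADSSS only, and half of it would remain in an estimate averaged over both orders.

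The expected consequences are more HEEADSSS positives and inflated agreement. In the illustrations, averaged kappa rises from 0.48 to between 0.54 and 0.59 when half of the YouthCHAT-only cases are picked up. The rate gap can move either way, and so can HEEADSSS time.

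These sizes rest on assumed cell rates, an assumed degree of influence and equal allocation. The halving needs only equal allocation and averaging over both orders.

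**What to change.** 1. **Conduct.** State that HEEADSSS present/absent is recorded for every domain before the YouthCHAT report is opened, in both conditions. Any safety exception is for the clinical team to set. This closes the staff-knowledge route and keeps the full paired sample. It costs one work instruction to the clinic.

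2. **Analysis.** Report detection, agreement and time by randomised order, with an instrument-by-order term. That term estimates cH + cY, whereas the bias in the average is (cH − cY)/2. Show it beside the per-tool contrasts: HEEADSSS in Condition 1 against Condition 2 estimates cH, and YouthCHAT in Condition 2 against Condition 1 estimates cY.

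3. **Sensitivity analysis.** For rates and time, give the first-administered comparison (YouthCHAT in Condition 1 against HEEADSSS in Condition 2).

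Items 2 and 3 need a few sentences of analysis text. The first-administered comparison is less precise than a paired one and cannot estimate within-student agreement. It should therefore support the paired analysis, not replace it; only item 1 protects agreement in Condition 1.

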### Power Calculation and Data Analysis

For the RCT component of the study, an estimated 150 Year 9 students will be randomly allocated to either Condition 1 (YouthCHAT first) or Condition 2 (HEEADSSS first). A power calculation shows that given 144 participants, there will be 90% power to detect differences between the two assessments assuming a mean duration of 15 minutes for YouthCHAT (SD 30) and 45 minutes for HEEADSSS assessment (SD 90).

Quantitative data will be analyzed using Microsoft Excel and Statistical Software Package (SPSS). Analyses will include basic descriptive statistics (eg, number of youth screened, YouthCHAT summary data, HEEADSSS summary data, demographic characteristics of the sample). Parametric data will be analyzed using *t* tests and analysis of variance (ANOVA). Nonparametric data will be analyzed using Wilcoxon signed-rank tests.

Qualitative data will be analyzed using a general inductive approach [33] with collated text analyzed to identify emerging themes, which will then be independently coded by 2 researchers with consensus reached by adjudication. Data analysis will be conducted at the end of 2017.

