## Methods

### Study Design

We will use a mixed-methods participatory action research approach to development and validation of a YouthCHAT mapped to all HEEADSSS domains, and assessment of the acceptability and utility of YouthCHAT at a tertiary pediatric hospital and a low-decile high school. A randomized controlled trial (RCT) with counterbalanced design will be conducted at the high school to assess the comparability of YouthCHAT and HEEADSSS.

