### Outcome Variables

The main study variables are (1) comparability (eg, is YouthCHAT at least as good or better than HEEADSSS assessment at detecting mental health and lifestyle issues among Year 9 youth? Is it a faster method of screening?), (2) acceptability (eg, is YouthCHAT content/format an acceptable alternative or companion to HEEADSSS assessment?), and (3) utility (eg, is YouthCHAT useful in helping to streamline assessment processes?).

Our primary outcome measures are (1) comparable detection rates for each domain for HEADSSS and YouthCHAT as measured by mental health or lifestyle issue “present” or “absent” (Tamaki sample only), (2) time taken to complete YouthCHAT and HEEADSSS screening (Tamaki sample only), and (3) acceptability and utility of YouthCHAT as assessed via feedback from staff and students/patients (Starship and Tamaki participants). Secondary outcome measures include differences in YouthCHAT versus HEEADSSS screening outcomes by gender and ethnicity.

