### Conclusion and Recommendations

If the outcomes indicate that YouthCHAT provides a comparable mental health and psychosocial assessment to HEEADDSSS, is acceptable to young people and clinical staff, and is faster to administer, we propose the following clinical changes.

All Year 9 students in low-decile high schools should be screened using YouthCHAT, and currently routine HEEADSSS assessments should not be undertaken where there is a negative screen. Instead, a tailored (targeted) HEEADSSS assessment should be conducted for the YouthCHAT positive domains.Young people with long-term physical conditions who are admitted to pediatric hospitals or attending routine outpatient clinics for long-term physical conditions should undergo an annual YouthCHAT screen, with targeted HEEADSSS assessment where needed.All students in New Zealand high schools should be screened using YouthCHAT annually.The potential for YouthCHAT to be used in other countries should also be explored.

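### Per-domain detection is a primary outcome, but the trial is sized on duration only; low-prevalence domains could not support a claim of comparability, and the conclusion makes no exception for them

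*Protocol article*

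**What the plan says.** The Study Design section of the protocol article states that a randomized trial "will be conducted at the high school to assess the comparability of YouthCHAT and HEEADSSS". Outcome Variables poses the detection question in non-inferiority terms: "is YouthCHAT at least as good or better than HEEADSSS assessment at detecting mental health and lifestyle issues among Year 9 youth". It then lists as the first primary outcome "comparable detection rates for each domain for HEADSSS and YouthCHAT", scored present or absent, and as the second "time taken to complete YouthCHAT and HEEADSSS screening".

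Power Calculation and Data Analysis gives one size justification: "there will be 90% power to detect differences between the two assessments assuming a mean duration of 15 minutes for YouthCHAT" (SD 30), with 45 minutes (SD 90) for HEEADSSS. Planned enrolment is about 150. The quantitative tests named are t tests, ANOVA and Wilcoxon signed-rank tests.

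Conclusion and Recommendations makes its proposals conditional on YouthCHAT proving comparable overall, acceptable and faster. One proposal is that "currently routine HEEADSSS assessments should not be undertaken where there is a negative screen", with a targeted interview kept for the domains that screen positive.

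**The concern.** A claim that one tool detects as well as another in a given domain needs enough students in whom that domain is positive on at least one tool. The size calculation does not address this, because it uses duration alone. YouthCHAT has ten domains plus three new ones, and the students are 13 to 14 years old. If some domains, such as problematic gambling, are uncommon at that age, only a handful of students would be positive. A test of difference would then rarely reach significance even if YouthCHAT performed badly, and the absence of a difference could be read as comparability.

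At stake is what a negative screen is taken to mean. The recommendations let it stand in for the routine interview, so the important error is a HEEADSSS-positive student whom YouthCHAT misses. In a sparse domain that is the error this trial is least able to see.

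**Working it through.** **Inputs from the protocol article.** 144 students in the power statement, about 150 enrolled; durations 15 (SD 30) and 45 (SD 90) minutes; 27% of high school students affected by anxiety and depression (Introduction). The Introduction's other prevalence, over 50% for hazardous drinking, is for age 18 and is not used.

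**Assumptions.** Prevalence on HEEADSSS of 2%, 5%, 10% and 20%; two-sided 5% level; an exact McNemar test, which suits paired present/absent data; YouthCHAT misses half of the HEEADSSS positives and adds none.

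**1. The plan's own figure.** The 90% is for duration. Power = Φ(30 / √((30² + 90²)/n) − 1.96).
- Two independent groups of 72: standard error √(9000/72) = 11.18; 30/11.18 = 2.68; power 76.5%.
- Each of 144 students measured on both tools, zero correlation: standard error √(9000/144) = 7.91; 30/7.91 = 3.79; power 96.7%.

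Neither gives 90%. This needs its own recheck, and nothing below depends on it.

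**2. Expected HEEADSSS positives** (144 × prevalence): 2% gives 2.9; 5% gives 7.2; 10% gives 14.4; 20% gives 28.8; 27% gives 38.9.

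**3. Chance that poor detection goes unseen.** With m discordant students, all HEEADSSS-only, the exact two-sided p-value is 2 × 0.5^m. For m = 5 this is 0.0625 and for m = 6 it is 0.031, so at least six missed positives are needed. With three positives in total, missing all three gives p = 0.25. The number missed is Binomial(144, prevalence/2), and the test is non-significant when it is 5 or fewer.

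| Prevalence | Mean number missed | P(non-significant), n = 144 |
|---|---|---|
| 2% | 1.44 | 99.7% |
| 5% | 3.6 | 85% |
| 10% | 7.2 | 27% |
| 20% | 14.4 | 0.3% |
| 27% | 19.4 | about 0% |

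With 150 students the 5% figure is 83%.

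**4. If YouthCHAT also finds cases that HEEADSSS does not.** With YouthCHAT-only positives equal to 10% of the prevalence, power in the same scenario is 9% at 5% prevalence, 38% at 10%, 77% at 20% and 90% at 27%. Such positives contribute to the comparison, but here they make a net shortfall harder to detect.

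**5. Precision at best.** If YouthCHAT flags every HEEADSSS positive, the exact (Clopper-Pearson) 95% lower limit for the proportion flagged is 29% for 3/3, 59% for 7/7 and 77% for 14/14.

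**6. The scale matters.** At 3% prevalence, a tool that missed every case and added none would differ from HEEADSSS by 3 percentage points. It would therefore lie inside a 5-point absolute margin. An absolute difference is uninformative in rare domains.

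**The case against.** Several points on the other side are sound. Time is itself a primary outcome, and Outcome Variables places speed under comparability, so sizing on duration is legitimate. The low prevalences are assumptions: the protocol gives none for the less common domains, and lifestyle items such as physical activity or diet need not be rare. In domains at 20% or more, the half-missed scenario with none added would almost always be detected. HEEADSSS is described as unvalidated for problem identification, so agreement with it is not sensitivity in the usual sense, and students positive on YouthCHAT alone also inform the paired comparison. A margin may sit in a full protocol or analysis plan not shown. That could set a criterion but could not add positives.

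A reader might infer that the trial exists only to show comparable detection, or that the plan commits to declaring every domain comparable. The text supports neither. Time belongs to the stated purpose, and the recommendations are conditional Discussion text, not an analysis rule. What stands is narrower: they rest on one overall judgement and state no exception for domains with too few positives.

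A fixed rule requiring, say, an 80% lower limit among HEEADSSS positives would not be a good remedy. With 17 positives all 17 must be flagged, and with 39 at least 37. At 90% true agreement the chance of passing is 0.9^17 = 17% and, from the binomial, 24%. A tool that flagged everyone would also pass.

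**Conclusion.** The concern holds in a limited form. Detection in each domain is a primary outcome with no size justification, and any domain at about 2% to 5% prevalence could not support a claim of comparability with 144 to 150 students. Under the half-missed, none-added scenario a difference test would be non-significant about 99.7% (2%) to 85% (5%) of the time. The problem is moderate at 10% (27%) and largely gone at 20% or more for that scenario. The result rests on the assumed prevalences and on some of the thirteen domains being uncommon at age 13 to 14.

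It does not show that the sample size is wrong for the trial as a whole, nor that common domains are uninformative. It shows that one overall comparability conclusion could cover domains for which the data say almost nothing.

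**What to change.** No more students are needed.

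1. In Power Calculation and Data Analysis, state that the size was set for duration and not for detection. Recheck the 90% separately and do not repeat it as it stands.
2. For each domain, report the paired 2x2 table (both tools, HEEADSSS only, YouthCHAT only, neither), with exact 95% intervals for the paired difference and for positive and negative agreement. Claim comparability only where the interval lies within a margin that the investigators pre-specify, on a scale that remains informative at low prevalence. Do not infer it from a non-significant difference test.
3. Report the other domains as inconclusive, and limit the comparability conclusion in Conclusion and Recommendations to domains that meet the criterion.

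The cost is wording and a little extra tabulation. The downside is real: the claim will cover fewer domains, possibly few, depending on the margin.
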